# Autologous bone marrow expanded mesenchymal stem cells in patellar tendinopathy: protocol for a phase I/II, single-centre, randomized with active control PRP, double-blinded clinical trial

**DOI:** 10.1186/s13018-019-1477-2

**Published:** 2019-12-16

**Keywords:** Tendinopathy; Mesenchymal stem cells; Platelet-rich plasma

## Abstract

**Introduction:**

Patellar tendon overuse injuries are common in athletes. Imaging may show a change in tissue structure with tendon thickening and disruption of the intratendinous substance. We wish to test the hypothesis that both autologous bone marrow expanded mesenchymal stem cells and autologous leukocyte-poor platelet-rich plasma (LP-PRP) implanted into the area of the disrupted tendinopathic patellar tendon will restore function, but tendon regeneration tissue will only be observed in the subjects treated with autologous bone marrow expanded mesenchymal stem cells.

**Methods and analysis:**

This is a single-centre, pilot phase I/II, double-blinded clinical trial with randomisation with active control. Twenty patients with a diagnosis of patellar tendinopathy with imaging changes (tendon thickening and disruption of the intratendinous substance at the proximal portion of the patellar tendon) will be randomised in a 1:1 ratio to receive a local injection of either bone-marrow autologous mesenchymal stem cells (MSC), isolated and cultured under GMP at T*he Institute of Biology and Molecular Genetics* (IBGM) (Spain) or P-PRP. The study will have two aims: first, to ascertain whether a clinically relevant improvement after 3, 6 and 12 months according to the visual analogue scale (VAS), Victorian Institute of Sport Assessment for patellar tendons (VISA-P) and dynamometry scales (DYN) will be achieved; and second, to ascertain whether the proposed intervention will restore tendon structure as determined by ultrasonography (US), Doppler ultrasonography (DUS), and innovative MRI and ultrasound techniques: Magnetic Resonance T2 FAT SAT (UTE, Ultrashort Echo TE) sequence and Ultrasound Tissue Characterization (UTC). Patients who are randomised to the P-PRP treatment group but do not achieve a satisfactory primary endpoint after 6 months will be offered treatment with MSC.

**Trial registration:**

NCT03454737.

## Background

Overload patellar tendon injuries are common in elite athletes (7 to 45%) and activities where repetitive jumping is required [1–4]. Pain may become recurrent and refractory to any conservative management, leading to a sports-related or occupational disability [5]. The pathogenesis of patellar tendinopathy is still elusive, but a failed healing response remains at its basis [6, 7]. At the time of surgery, typically no inflammatory cells or inflammatory mediators are detected in the tendon tissue, suggesting that tendinopathy is not the result of typical inflammation [8, 9]. Poor vascularization is often reported as a factor that contributes to tendinopathy, but tendinopathy is often associated with neovascularization and increased blood-flow through the tendon, which might be a restorative and beneficial response [10]. Although the source of pain has not been defined [11], in some studies small substance P-positive nerve fibres are closely related to the neovascularization process and may transmit pain perception [6, 12–14].

Other pathological changes related to patellar tendinopathy include (a) intra-tendinous calcification; (b)accumulation of adipose cells; (c) disruption and disorganisation of collagen fibres; (d) conversion of type I collagen to type III collagen; (e) a reduction in number of fibroblasts; (f) changes in tenocyte morphology; and (g) an increase in proteoglycan and glycosaminoglycan content [6].

Although the accepted standard treatment for patellar tendinopathy is a graded rehabilitation programme, not all patients respond to exercise therapy [15]. Medical or surgical management may provide improvement in symptoms but does not result in regeneration of normal tendon tissue [16]. Recently, MSC have been shown to promote tendon healing in an animal model of acute tendon injury [17, 18]. In addition, these cells may control inflammation by influencing differentiation, migration or apoptosis in different immune cells [19–25].

MSC have the following distinctive features: (a) ability to differentiate into osteoblasts, adipocytes and chondrocytes in vitro; (b) ability to adhere to plastic during culture; (c) more than 90% of the cells show a positive immunophenotype for CD73, CD105, CD90 and CD166 antigens; less than 10% of the cells show a positive immunophenotype for CD45, CD14, CD34, CD31 and HLA-DR antigens [26]. MSCs are found in several organs and tissues, where they may be harvested. Nevertheless, bone marrow is the optimal and most easily accessible source of MSC. Once obtained, these cells can be isolated and grown *ex vivo* under pharmaceutical standards and used in human therapies known as an ‘advanced therapy medicine’ [27]. Our research group has used MSC successfully in several osteoarticular injuries [28–36]. Given the immunomodulatory and anti-inflammatory abilities of MSC, harvesting and grafting these cells into an area affected by patellar tendinopathy are feasible options that may provide satisfactory results.

The use of autologous leukocyte-poor platelet-rich plasma (LP-PRP) in tendon injuries is well established [37], including patellar tendon injuries, at times showing good clinical response [38, 39]^.^ Our research group has also successfully used this approach in various musculoskeletal conditions in several areas of the human body [40, 41]. A recent systematic review and meta-analysis [42] demonstrated improved outcomes with the use of leukocyte-rich-PRP (LR-PRP) compared to LP-PRP.

We wish to test the hypothesis that an analgesic effect will be achieved using either treatment, but significant regeneration of tendon tissue will only be achieved in the cell therapy group. We will assess clinical results by clinical examination, visual analogue scale (VAS), the validated Spanish version of VISA-P^43^ and manual dynamometry. We will evaluate tissue regeneration using several imaging techniques. The use of MRI with a UTE sequence in the sagittal plane makes it possible to determine tendon tissue features at very low T2 values in all regions, including the ‘gap’ and healthy tendon tissue. In addition, UTE sequences allow to visualize and delineate defects that are not detected by conventional imaging.

UTC is an innovative imaging technique for assessing tendon injuries. Using a conventional ultrasound device, 600 axial sections of the tendon are performed at 0.2 mm intervals and compounded to form a 3D image. Using this technique, collagen fibre alignment may be quantified into four different types: (a) normal aligned fibrillar structure; (b) slightly misaligned fibrillar structure; (c) disorganised fibrillar structure; (d) complete disintegration of tendon tissue [43]. Ultrasonography is the most accessible imaging technique used to confirm the clinical diagnosis and determine the exact location of the lesion. Ultrasonography also helps calculate tendon size, defines eco-texture, allows measurement of any tendon gaps in several planes and assesses the degree of tendon vascularization. In addition, ultrasonography allows to dynamically monitor tendon function [44].

Should the results be better for the cell therapy group, the patients in the active control group (who were injected with LP-PRP) who have not achieved similar benefits to those of patients in the MSC group after 6 months will be offered cell therapy. We believe that this will increase the feasibility of the clinical trial.

### Characteristics of the MSC intervention

MSCs exhibit the typical stem cell features defined by the International Society of Cellular Therapy [23]. MSC are an advanced therapy drug registered with the *Agencia Española de Medicamentos y Productos Sanitarios* (AEMPS) with IND number 10–134. They are bone marrow MSC, processed according to the GMP practices at the IBGM and re-suspended in an isotonic medium composed of Ringer lactate solution, 0.2% human serum albumin and 5mM glucose. The product is supplied by the laboratory after a 23-day processing period. Cell viability is ≥ 90%, and negative microbiological results are obtained for Gram and Mycoplasma microorganisms. Endotoxin levels are below 0.5 IU/mL. The product is stable for 8 h at 4–12 °C. The product is supplied in two 5 mL syringes, one containing 10 × 10^6^ MSC suspended in a 2 mL solution, and the other containing 10 × 10^6^ MSC suspended in a 4 mL solution. The total dose of cells supplied is 20 × 10^6^ ± 2 × 10^6^ MSC.

### General characteristics of P-PRP intervention

LP-PRP is obtained under strict aseptic conditions. Blood components are fractioned by centrifugation. In a surgical environment, peripheral venous blood is collected into four 9 mL citrate tubes. The anticoagulated blood is centrifuged at 1,200 rpm for 8 min (460*g*). Six milliliters of LP-PRP are obtained from a 36-mL sample of autologous peripheral venous blood. The LP-PRP suspension contains a two-fold increase in the number of platelets compared to peripheral blood and a very low number of leukocytes (average basal peripheral blood 228 × 10^3^ platelets/mm^3^, range 165–329 × 10^3^; LP-PRP: 563 × 10^3^ platelets/mm^3^; range 407–801 × 10^3^). Before application, plasma coagulation is activated by adding 5% CaCl2 [38, 45].

## Methods/design

### Main objectives

To assess the clinical efficacy of MSC injection and compare the results with those obtained in the LP-PRP group. Outcomes will be assessed using subjective patient reports, VAS and VISA-P scales, and strength determination of the extensor muscle group using manual dynamometry (DYN).To confirm changes in the architecture for regeneration of the patellar tendon gap following peritendinous and intratendinous injection of MSC and compare these results with those obtained in the LP-PRP group. Assessment will be performed using UTE-MRI, UTC and ultrasonography.

### Secondary objectives

To assess the viability and safety of the use of medical devices MSC and LP-PRP when injected into the patellar tendon; prove that all procedures described in the present protocol are feasible; and register potential adverse events related to either treatment, as well as any other adverse events that occur during the clinical trial, whether related to the trial or not.

### Trial design

#### Study population

Twenty male recreational athletes with a patellar tendinopathy who meet the inclusion and exclusion criteria will be recruited and will be followed for 1 year (Fig. 1).

**Fig. 1 Fig1:**
[figure not shown]
Study flow chart

Inclusion criteria:
Male participants aged between 18 and 48Pain and tenderness at the area of attachment of the patellar tendon on the lower pole of the patella [46] for more than 4 months, with no clinically relevant response after conservative treatmentsUS confirming disruption ≥ 3 mm of the fibrillar structure in the proximal portion of the patellar tendon, tendon thickening and a hypoechoic injury MRI of the patellar tendon in T2 FAT SAT sequence (fat saturation) showing an increase of ≥ 3 mm in longitudinal diameter at the proximal insertionInformed signed written consent by the participantThe participant is able to understand the nature of the study.

Exclusion criteria:
Participant younger than 18 (or legally dependent) or over 48 years of ageMRI with a grade III–IV osteochondral lesion in any compartment of the kneeInjury to the anterior or posterior cruciate ligamentLocal injection with corticosteroid during the previous 12 monthsLocal injection with PRP during the previous 6 monthsEvidence of local or systemic infectionPatients presenting with positive serology to HIV 1 or 2, hepatitis B (HBsAg, HBcAc), hepatitis C (anti-HCV-Ab) and syphilisCongenital or acquired conditions involving malformation and/or significant deformation of the knee that hampers the administration of the planned intervention and evaluation of the resultsBody mass index (BMI) greater than 30. 5 (obesity grade II)Active neoplastic diseaseImmunosuppressionSimultaneous participation in another clinical trial or treatment with another research product during the 30 days prior to inclusion in the studyOther pathologies or circumstances that may compromise participation in the study according to medical criteria.

Patients will be randomized by the Clinical Research Organization (CRO) (Adknoma) using SAS statistical software (version 9. 4) into either the MSC group or PRP group in a 1: 1 ratio. After randomization, either MSC or LP-PRP will be injected intralesionally and around the affected area of the patellar tendon. To keep patients and evaluating physicians blind to treatment, sham procedures will be performed in both groups (i.e. the MSC group will have blood extracted and will have their tendon injected with normal saline at the first stage of treatment, and the LP-PRP group will undergo a sham bone marrow harvesting at the first stage of treatment). The treating physicians will not be blind to the treatment administered.

### Experimental phase A

#### MSC treatment group

Ten patients will be treated with saline solution (sham) and with 20 × 10E^6^ MSC after 23 days.

##### Stage one

Under sterile conditions, a total of 4 citrate tubes (9 mL per tube; total volume 36 mL) of venous blood are withdrawn from the antecubital vein of the non-dominant arm as a sham procedure of P-PRP preparation.With the patient prone, and after sedation induced by midazolam and propofol, local anaesthetic injections (lidocaine 1%; 10 mL) are administered in both the posterior superior iliac crests and are penetrated using an 11 gauge trocar. Using sequential aspirations of 1–2 mL each, 100 mL of bone marrow is collected in a heparinized container to be sent to IBGM for isolation and culture of MSC.The patient is then positioned supine. Under ultrasonography guidance, 1 mL of normosaline solution is injected using a 22 gauge needle in the tendinous and 1 mL in the paratendinous medial and lateral areas of the patellar tendon. The participant is then transferred to the postoperative recovery room, where they remain for 1 h before discharge.

##### Stage two (after 23 days)

Under sterile conditions, a total of 4 citrate tubes (9 mL per tube; total volume 36 mL) of venous blood are withdrawn from the antecubital vein of the non-dominant arm as a sham procedure of P-PRP preparation.With the patient supine under sedation with midazolam and propofol, under ultrasonography guidance, a 2-mL solution containing 10 × 10^6^ MSV is injected into the tendon; a 2-mL solution containing 5 × 10^6^ MSC is injected into the medial peritendinous area, and a 2-mL solution containing 5 × 10^6^ MSC is injected into the lateral peritendinous area.

#### LP-PRP control group

Ten patients will be treated with two doses of LP-PRP, each containing 6 mL of solution-PRP. The second dose will be injected 23 days after the first one.

##### Stage one

Under sterile conditions, a total of 4 citrate tubes (9 mL per tube; total volume 36 mL) of venous blood are withdrawn from the antecubital vein of the non-dominant arm for P-PRP preparation. One to two supplementary tubes of peripheral venous blood are withdrawn for preservation in a serum bank for security reasons. LP-PRP is prepared according to ITRT’s PRP protocol.With the patient prone, and after sedation induced by midazolam and propofol, 10 mL of lidocaine 1% is administered in the posterior superior iliac crests, and an 11-gauge trocar is inserted in the subcutaneous tissue as part of the sham procedure for obtaining MSC.With the patient supine, and sedation induced by midazolam and propofol, using ultrasound guidance, 2 mL of LP-PRP are injected intratendinously, 2 mLof LP-PRP are injected into the medial peritendinous area, and 2 mL of LP-PRP are injected in the lateral peritendinous zone adjacent to the area of tendinopathy.

##### Second stage (after 23 days)

The procedure for obtaining blood and LP-PRP preparation is performed again under sterile conditions.With the patient supine, and sedation induced by midazolam and propofol, using ultrasound guidance, 2 mL of LP-PRP are injected intratendinously, 2 mL of LP-PRP are injected into the medial peritendinous area, and 2 mL of LP-PRP are injected in the lateral peritendinous zone adjacent to the area of tendinopathy.

### Experimental phase B

Results will be evaluated 6 months after the treatment. If the results support the hypothesis that a higher efficacy is obtained in the MSC group, the cell therapy trial will be offered to subjects from the LP-PRP group who show no evidence of clinically relevant improvement: if they wish, this group will be treated with MSC. This will be ‘experimental phase B’, which will be evaluated with the same clinical and imaging assessment protocol as described above.

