### Response evaluation

Subsequent assessments following the treatment include AE review, VAS (pain), VISA-P Questionnaire, ultrasound imaging (conventional ultrasound, UTC and MRI), dynamometry manual test and clinical assessment (Table 2 for phase A, and Table 3 for phase B). These will take place at 1, 2, 3, 6, 8 and 10 weeks and 3, 6, 12 months post-treatment.

**Table 2 Tab2:** Outcome assessments experimental phase A

Study period															
	Enrollment				Treatment		Follow-up								
Timepoints					0	23 days	1 week	2 weeks	3 weeks	6 weeks	8 weeks	10 weeks	3 months	6 months	12 months
Inf. sheet	X														
Incl/excl Criteria		X													
IC		X													
Preop + serology			X												
Allocation				X											
ClinicalHistory	X	X													
Physical exam	X	X					X	X	X	X	X	X	X	X	X
VAS		X					X	X	X	X	X	X	X	X	X
VISA-P		X					X	X	X	X	X	X	X	X	X
blood test													X		
Group MSV BM					X										
Group MSV saline sol.					X										
Group MSV MSV						X									
Group PRP BM sham					X										
Group PRP PRP					X	X									
Bloodbank					X										
MRI		X											X*		X
Ultrasound		X					X	X	X	X	X	X	X	X	X
UTC			X						X		X		X	X	X
DYN			X						X		X		X	X	X
AE					X	X	X	X	X	X	X	X	X	X	X
Medication					X	X	X	X	X	X	X	X	X	X	X

*Elig.* eligibility, *IC* informed consent; *VAS* visual analogue scale; *VISA-P* Victorian Institute of Sport Assessment (Patellar); *BM* bone marrow harvest; MSC Infusion of MSC; *MRI* magnetic Rresonance; *UTC* ultrasound tissue characterisation; *DYN* dynamometry, *PreOp* preoperative study, *AE* Adverse Events.

*X** if the *VAS* and *VISA-P* scales show a significant improvement, and *MRI*, *US*, and UTC provide evidence of healing, the result will be considered positive and the patient will be followed up with confirmation controls at 6 and 12 months. For safety reasons, according to AEMPS criteria, a control test will be performed after the trial, within a period of 2 years after treatment.

If the 6-month evaluation shows negative results, patients may be transferred to the open experimental phase B.

**Table 3 Tab3:** Outcome assessments experimental phase B

Study period															
	Enrollment			Treatment		Follow-up									
Timepoints				0	23 days	1 weeks	2 weeks	3 weeks	6 weeks	8 weeks	10 weeks	3 months	18 weeks	6 months	12 months
IC		X													
Preop + serology			X												
Physicalexam	X	X				X	X	X	X	X	X	X	X	X	X
VAS		X				X	X	X	X	X	X	X	X	X	X
VISA-P		X				X	X	X	X	X	X	X	X	X	X

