### Statistical analysis

Statistical analysis will be performed using version 21. 0 of the Statistical Package for Social Sciences (SPSS Inc, Chicago, IL). We will evaluate: (i) adverse events (AE) and serious adverse events (SAE) showing relationships, causality and severity will be provided; (ii) frequency and percentage of AE and SAE; (iii) laboratory results including hematologic and biochemistry values will be collated: leukocytes levels, absolute neutrophils count, platelet count, creatinine levels, AST (SGOT)/ALT (SGTP) levels, etc. A list of laboratory parameters will be obtained for each patient and visit and will include reference range values. Values will be summarized in a basal and post-basal visit analysis will include the following values: (i) valid ‘n’; (ii) mean; (iii) standard deviation; (iv) median; (v) minimum and maximum.

The frequency and percentage values of patients showing evidence of tendon regeneration 6 months after treatment with MSC or P-PRP will be provided.

The following methods will be used to describe and analyse the results obtained:
Descriptive statistics in numerical variables: number of valid cases; number of non-available values; mean value; standard deviation; 95% confidence interval for the mean value; median, minimum and maximum values. In discrete and categorical variables, the following values will be provided: frequency; percentage value for the total number of valid cases; percentage value for the total number of non-available values.Inferential statistics tests for comparing groups and time points: ANOVA with repeated measures (or ANCOVA) if covariables with a significant interaction are detected with their corresponding contrast values (Scheffe test), or non-parametric tests if the assumption of normality is rejected (Mann-Whitney *U* test for comparison between groups and Wilcoxon test for comparison between measurements). The significance level for all statistical analyses will be 0. 05.

Efficiency sample (per protocol (PP) population) includes all patients whose tendon lesion has been treated with an MSC or LP-PRP suspension. These patients must have had no major violations of the protocol, and at least one assessment of efficacy after treatment.

‘Full analysis set’ (FAS) (intention to treat analysis) includes all patients in the study, whether they finish the study or comply with the protocol.

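### Once any LP-PRP non-improver takes MSC in phase B, the month-12 between-arm comparison is no longer MSC versus LP-PRP, and the plan does not end that comparison at month 6

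*Protocol article*

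**What the plan says.** All references are to the protocol article.

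**Month 12 is an efficacy time point, and efficacy is comparative.** The first aim in the abstract (Methods and analysis) is to learn "whether a clinically relevant improvement after 3, 6 and 12 months according to the visual analogue scale", VISA-P and dynamometry. Main objectives: "To assess the clinical efficacy of MSC injection and compare the results with those obtained in the LP-PRP group". All 20 patients are followed for one year (Study population). Table 2 schedules VAS, VISA-P, ultrasound, UTC, dynamometry and MRI at month 12. The top VISA-P grade, 80 or more, is defined only at month 12 (Pain and function).

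**From month 6 one arm may change treatment.** Experimental phase B: if the 6-month results favour MSC, "the cell therapy trial will be offered to subjects from the LP-PRP group who show no evidence of clinically relevant improvement". The Table 2 footnote (Response evaluation) says that after a negative 6-month evaluation "patients may be transferred to the open experimental phase B". The Discussion also calls this phase open.

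**Analysis.** Groups and time points are compared by repeated-measures ANOVA or ANCOVA, or by Mann-Whitney and Wilcoxon tests (Statistical analysis). The full analysis set "includes all patients in the study, whether they finish the study or comply with the protocol". The per-protocol set requires treatment, no major violation and at least one efficacy assessment after treatment. No passage stops the between-arm test at month 6 or says how month-12 values of crossed patients enter it.

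**The concern.** Crossover is limited to LP-PRP patients and triggered by a poor month-6 outcome. After it, the LP-PRP column at month 12 is either a mixture of LP-PRP and LP-PRP followed by MSC, or a subset chosen for having done well on LP-PRP. Neither is the randomised comparator that the objectives name.

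The offer also tells the patients who receive it that they were given LP-PRP. Their later VAS and VISA-P scores are self-reported by people who know their allocation, in a trial that uses sham blood draws, sham marrow harvesting and saline injection to prevent this.

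At stake is any controlled statement about month 12, including the VISA-P grade of 80 or more. It also affects MRI: as Table 2 reads, phase A MRI is done at baseline, month 3 and month 12, with none at month 6.

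**Working it through.** **No figure to reproduce.** The article gives no SD, power calculation or expected crossover rate. The structural point rests on reading the sections together; the arithmetic only illustrates its size.

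**1. Sections side by side**

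| Question | What the article fixes |
|---|---|
| Are arms compared at month 12? | Yes: abstract aim, Main objectives, Table 2 and Statistical analysis together |
| Who may switch? | LP-PRP patients without adequate improvement at month 6; the Table 2 footnote names no arm |
| Is the offer conditional on group results? | Background and Experimental phase B: yes. Abstract: no such condition |
| Is the phase after switching blinded? | No, it is open |
| Is the between-arm test stopped before switching? | Not stated anywhere |

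**2. Inputs**

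- From the article: 10 patients per arm; usual VISA-P of 30 to 50 in chronic disease, used as baseline b; minimum difference of 13 points, used here to represent lack of clinically relevant improvement.
- Assumed: LP-PRP month-6 mean 60 or 65, flat to month 12 without MSC; SD of gain 18; correlation r between month-6 and month-12 gains 0.5 to 0.7; true MSC advantage 10 points; every eligible patient crosses and gains the full 10 points by month 12.

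**3. Formulas**

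Mean LP-PRP gain g = month-6 mean − b, and z = (13 − g)/18.

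- Share crossing: c = Φ(z).
- As-randomised difference at month 12: 10 × (1 − c).
- Difference with crossed patients dropped: 10 − r × 18 × φ(z)/(1 − c). The subtracted term is the expected excess at month 12 of patients selected for gaining at least 13 at month 6.

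**4. Results**

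| Month-6 mean | Baseline | g | c | As randomised | Crossed dropped (r 0.5; r 0.7) |
|---|---|---|---|---|---|
| 65 | 30 | 35 | 11% | 8.9 | 8.1; 7.3 |
| 60 | 30 | 30 | 17% | 8.3 | 7.2; 6.1 |
| 65 | 40 | 25 | 25% | 7.5 | 6.2; 4.6 |
| 60 | 40 | 20 | 35% | 6.5 | 4.9; 2.8 |
| 65 | 50 | 15 | 46% | 5.4 | 3.4; 0.8 |
| 60 | 50 | 10 | 57% | 4.3 | 1.8; −1.4 |

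For the last row: z = 3/18 = 0.167, c = 0.566, and 10 × 0.434 = 4.3. With φ(z) = 0.393, 0.393/0.434 = 0.907, so 10 − 0.7 × 18 × 0.907 = −1.4.

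In an arm of ten, 11% to 57% is roughly one to six patients. Neither way of handling them returns the true 10 points.

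**The case against.** **The offer may never be made.** Background and Experimental phase B open it only if 6-month results favour MSC, and only to patients who want it. If opening it required month-6 data on all 20 patients, early entrants might complete month 12 first, since recruitment ran from December 2017 to October 2018. This stands as a limit on frequency and size, and is why the point is conditional. It does not remove the conflict: the abstract states no such condition, and where the condition applies, crossover opens when MSC looks better, which is when a month-12 comparison would be wanted.

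**Handling of crossed data is SAP content, and a valid analysis exists.** The as-randomised month-12 contrast is legitimate as a treatment-policy comparison. Alternatively, post-crossover values could be set missing and modelled given month 6. If crossing depends only on the observed month-6 score, that recovers about 10 points in simulation. Both are fair. But the first answers a different question from the stated objective. The second depends on a model that ten patients per arm can hardly support, and on crossing being fully explained by recorded data, although response is judged on several measures and the patient chooses. Neither restores a blinded randomised contrast.

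**Stronger readings that the document does not support.**

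- A reader might infer that both analysis sets keep crossed patients in the LP-PRP column and that adverse events after MSC count against LP-PRP. Neither is stated. Phase B has its own time zero, schedule and adverse-event rows (Table 3).
- A reader might infer that the whole trial is unblinded after month 6. Open describes phase B. Allocation is revealed to patients who receive the offer; unblinding of evaluators or other patients is possible but not stated.
- A reader might take VISA-P below 70 as the crossover rule, which would give 61% to 71% crossing and a difference of 2.8 to 3.9. Pain and function uses 70 as a grade of success at 6 months. Experimental phase B uses lack of clinically relevant improvement, and a patient rising from 40 to 65 has gained 25 points.

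**Conclusion.** The point holds conditionally. If any LP-PRP patient crosses, the month-12 contrast is not MSC versus LP-PRP, and the plan as written does not exclude it from between-arm testing. That conclusion rests on the text alone.

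The size rests on assumptions: about 4.3 to 8.9 points as randomised and about −1.4 to 8.1 with crossed patients dropped, against a true 10. Full uptake and full effect are assumed, and less of either means less dilution. The change of sign appears only at the extreme of the range (baseline 50, month-6 mean 60, correlation 0.7) and should not be presented as the expected result.

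The 3- and 6-month comparisons are unaffected, as are the 6-month regeneration summary and the 6-month non-response criteria.

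**What to change.** 1. State that month 6 is the last between-arm test of MSC versus LP-PRP, that all month-6 assessments are completed before any allocation is revealed, and that month 12 is removed from the group-by-time test.
2. Report month 12 descriptively: durability in the MSC arm, and the LP-PRP arm as randomised, labelled as LP-PRP with optional MSC (a treatment-policy comparison).
3. State that efficacy and adverse-event data after crossover MSC are reported under phase B, as LP-PRP then MSC, and not as LP-PRP.
4. Reconcile the differing conditions for the offer in the abstract, Background, Experimental phase B and the Table 2 footnote: whether group results must favour MSC first, which patients are eligible, and on what measure.

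**Cost.** Wording only; no extra patients or visits. The sponsor gives up a controlled 12-month MSC versus LP-PRP claim, which the design cannot support once patients cross. As Table 2 reads, the last MRI before crossover opens is then month 3. Recruitment was complete by October 2018, so the step on completing assessments before allocation is revealed may come too late for some patients. The analysis and labelling changes do not depend on it.
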